## Abstract

**Context:**

According to the World Health Organization, alcohol is a major global public health problem, leading to a significant increase in illness and death. To treat alcohol use disorders, new therapeutic tools are being promoted, among which virtual reality (VR) shows promise. Previous research has demonstrated the efficacy of VR in reducing alcohol cravings in patients, but there is a lack of data on its effectiveness in maintaining abstinence or reducing consumption in recently abstinent individuals.

The E-Reva study aims to compare the efficacy of a treatment strategy combining virtual reality cue exposure therapy (VR-CET) and cognitive behavioral therapy (CBT) with conventional CBT in reducing alcohol consumption and craving in patients with alcohol use disorder (AUD). In addition to this primary objective, the study will compare the effects of VR-CET combined with CBT on anxiety, depression, rumination, and feelings of self-efficacy versus conventional CBT.

**Methods:**

This prospective randomized controlled trial will be conducted over 8 months in four addiction departments in France. It includes two parallel groups: i) the VR-CET + CBT group, and ii) the CBT-only group, which serves as a control group.

Participants will be recruited by the investigating doctor in the addiction centers. The sample will consist of 156 patients diagnosed with AUD and abstinent for at least 15 days.

Both treatment groups will participate in four group CBT sessions followed by four individual sessions: i) the VR-CET group will be exposed to virtual environments associated with alcohol-related stimuli, ii) the CBT-only group will receive traditional CBT sessions. After completion of the 8 sessions, patients will be followed up for 6 months. The primary outcome is the cumulative number of standard drinks consumed at 8 months, assessed using the TLFB method.

**Discussion:**

Despite the promise of VR-CET to reduce the desire to drink, the effect on alcohol consumption remains uncertain in the existing literature. Our protocol aims to address the limitations of previous research by increasing sample size, targeting consumption reduction, and incorporating neutral environments. E-Reva aims to enrich the literature on the use of VR in the treatment of AUD and open new perspectives for future interventions.

**Trial registration:**

ClinicalTrials.gov ID NCT06104176, Registered 2023/11/13 (https://clinicaltrials.gov/study/NCT06104176?id=NCT06104176&rank=1).

N° IDRCB: 2022-A02797-36.

Protocol version 1.0, 12/05/2023.

**Supplementary Information:**

The online version contains supplementary material available at 10.1186/s13063-024-08271-x.

## Introduction

Responsible for nearly 3.3 million deaths per year, alcohol has been a worldwide public health problem for years [1, 2]. The ethanol (ethyl alcohol) in alcohol is responsible for numerous disorders: cognitive and behavioral disorders, certain types of cancer, cardiovascular disease, higher risk of cirrhosis and pancreatitis, and trauma from violence and road or work accidents [3]. Excessive alcohol consumption therefore induces neurobiological and behavioral changes, creating a breeding ground for the development of alcohol use disorder (AUD). According to the 5th version of the Diagnostic and Statistical Manual of Mental Disorders, AUD is defined as "a set of behavioral, cognitive, and physiological phenomena that result in progressive disinvestment from other activities" [4]. Despite the harmful physical and emotional effects of excessive alcohol use, many people find it difficult to reduce or maintain abstinence over the long term [5].

Craving is defined as "a compelling need to consume the substance" that can lead to compulsive substance seeking and consumption-related behaviors. Craving elicits psychophysiological, emotional, cognitive, and behavioral responses that follow a subjective perception of the urge to drink alcohol [6]. Craving is a key element in the development and maintenance of excessive drinking and AUD [7, 8].

Treatment for AUD is based on a multidimensional approach that includes pharmaceutical, behavioral, and psychosocial interventions [7]. These treatments aim to address loss of control over use, reduce negative emotions and hyperreactivity to stress, and/or reduce craving [9]. Among these interventions, several meta-analyses conclude that CBTs are effective in treating addictive disorders, have few contraindications, and are easy to implement [10, 11].

One of the tools used in CBTs is cue exposure therapy (CET), which aims to teach craving self-management techniques through in vivo, in imagination, or multimedia exposure to substance-related stimuli [7, 12]. CET is based on the principles of deconditioning a behavior considered maladaptive to replace it with one considered more adaptive, and systematically desensitizing the subject by immersing him or her in the anxiety-provoking environment. Despite its success in treating anxiety disorders, CET has shown limited results in reducing alcohol consumption [13]. This limited effectiveness appears to be related to the ecological validity of the cues used [12, 13]. The in vivo exposures proposed in CET are costly and complex to replicate, as they require specific environments and situations (e.g., bars, nightclubs…). Consequently, exposures are often performed in the laboratory, but these experimental approaches involve artificial behavioral responses to simple stimuli, with constraints on the modification of parameters, context, and available space, which limits the complexity of behavioral interactions [8, 14].

Virtual reality exposure therapy (VR-CET) is a new therapeutic exposure technique that uses virtual reality (VR) to allow users to navigate and interact with a computer-generated (and computer-maintained) three-dimensional environment in real time through a headset [15]. The advantages of this technique are the therapist's control over the exposure, the freedom to stop exposure at any time if necessary, the possibility of adapting the virtual environment to the subject's problems, and better observation of the patient's reactions. All these elements promote greater immersion and interaction of the patient with the virtual environment than, for example, exposure in imagination, another typical technique used in CBT [16]. Moreover, technological advances in recent years have made it widely available, easily accessible, simpler to use, better tolerated, and increasingly less expensive. Several studies report promising results for VR-CET in the treatment of various mental disorders [16], including addictive disorders [17]. The use of virtual reality was motivated by the fact that many patients were reluctant to experience violent anxiety-provoking situations in vivo during CBT sessions [18]. Thus, the application of VR-CET has been extended to many other specific phobic disorders (acrophobia, arachnophobia, social phobia, claustrophobia, agoraphobia,etc.) and has shown a therapeutic effect superior to no intervention and equivalent to exposure through standard techniques [18–20]. For people suffering from excessive alcohol consumption, VR-CET has been shown to be effective in inducing and reducing craving [21]. Despite this promising advance, there remains a gap in the data on the efficacy of VR-CET in maintaining abstinence or reducing alcohol consumption, which remain the primary goals of therapeutic interventions. This raises the need for further studies to shed light on this area of research. The primary objective of this study is to evaluate the efficacy of a treatment strategy combining VR-CET and CBT on reducing the cumulative number of standard drinks (sd) of alcohol at 8 months after enrollment. Secondary objectives are to evaluate the efficacy of the same treatment strategy on reducing alcohol craving, anxiety, depression, and rumination, and on increasing self-efficacy at 8 months. This article describes, in accordance with SPIRIT standards [22] and following the CONSORT [23] declaration checklist A prospective, comparative, randomized, open-label, 8-month clinical trial (2 months of therapy followed by 6 months of follow-up) with two parallel groups: i) VR-CET + CBT, ii) CBT alone without exposure (control group). This was a national multicenter study involving four addictology centers. A total of 156 patients diagnosed with AUD according to DSM-5 criteria were included.

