### Study design and procedure

This study is a multi-center, randomized, controlled trial involving two parallel groups: i) the VR-CET group, which benefits from virtual reality exposure preceded by CBT sessions, and ii) the CBT-only group (control group). Interventions take place over a 2-month (8-week) cycle, with a total of 8 sessions (Cf. Figure 1). Both groups receive 4 CBT group sessions in the first month, followed by either 4 supervised individual virtual exposure sessions for the VR-CET group, or 4 additional individual CBT sessions for the CBT-only group. Each session lasts one hour and a half. Once the 8 sessions have been completed (2 months), patients are followed up for 6 months, for a total of 8 months.

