### Treatment groups

The first four CBT group sessions focus on understanding the effects of alcohol, assessing motivation to change, behavioral and emotional strategies, cognitive strategies, relapse prevention and assertiveness strategies. These sessions are conducted in a group setting by a trained psychologist and a trainee.

Participants are then randomized into two groups (M1): i) VR-CET + BT group, ii) CBT group only. Allocation is centralized, individualized and randomized according to the following factors: center, presence of pharmacological treatment to maintain alcohol abstinence (2 modalities), history of AUD treatment in the last five years (2 modalities), alcohol consumption goals (2 modalities) and severity of alcohol dependence according to DSM-5 criteria (3 modalities).

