### Evaluation outcomes

#### Primary outcome

The primary outcome is the cumulative number of standard drinks consumed (in grams of pure alcohol) at 8 months, as reported by patients. As a reminder, in France, 1 standard drink = 10 g of pure alcohol = 1 unit of alcohol [25]. Alcohol consumption is estimated retrospectively by patients every month using the Timeline Follow-Back (TLFB) method, a widely used method that has demonstrated good psychometric properties and superiority over free recall [26]. This method allows retrospective estimation of alcohol consumption over a specified period of up to one year. Estimates of alcohol consumption (in standard drinks) are collected monthly by the research team, either in person or by telephone, to reduce recall bias and improve the performance of this method over time [27].

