### Sample size

To determine the number of participants needed for the study, we randomly selected 15 patients with alcohol-related disorders (AUD) who were already being treated at the Albert Chenevier Day Hospital's addiction department. Their cumulative alcohol consumption was monitored at two, five and eight months after admission to estimate the average daily consumption over eight months. The target consumption was calculated on the basis of the recommendations of the European Medicines Agency [39], aiming at a reduction of at least two risk levels according to the World Health Organization. To achieve a statistical power of 0.8, considering a risk α of 0.05 with a two-sided hypothesis, 65 patients per group are required. Assuming a drop-out rate of 20%, 78 patients per group need to be recruited, for a total of 156 patients for both groups. See Table 2 for recruitment procedure.

**Table 2 Tab2:** Recruitment procedures

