### Statistical methods

The characteristics of all patients will be described globally and according to their randomization group, using the number of patients (%) for qualitative variables and the median [interquartile range] or mean (± standard deviation) for quantitative variables, depending on the normality of their distribution. A patient flow diagram will be generated. Results are reported according to CONSORT recommendations. Tests will be two-tailed, and a significance level of *p* < 0.05 will be considered statistically significant. The primary outcome (self-reported cumulative number of standard drinks consumed at 8 months) will be compared between the two groups using Student's t-test for independent samples. Complementary analyses will be conducted using generalized linear regression models adjusted for minimization factors and number of sessions per setting. Given the repeated measurement of outcomes and the multicenter design of the study, additional analysis will be performed including Cox and mixed models. To consider Survival analysis will also be conducted using a linear mixed model. Secondary endpoints will be analyzed using the same methodology as for the primary endpoint, i.e. a comparison of the mean using the usual tests. primary endpoint, i.e. a comparison of means using standard tests at 8 months. Secondary analyses to assess changes in secondary endpoints will be performed using evaluated using linear mixed models.

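### The primary outcome counts drinks from enrolment, but allocation is at M1: about one of the eight months cannot respond to treatment and costs power by an amount the protocol does not let one fix

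*Protocol article*

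**What the plan says.** All places are in the protocol article.

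- **Outcome window.** The Introduction gives the primary objective as "reducing the cumulative number of standard drinks (sd) of alcohol at 8 months after enrollment". The Primary outcome section says "The primary outcome is the cumulative number of standard drinks consumed (in grams of pure alcohol) at 8 months" and names no start point. It states that drinking is estimated every month by TLFB.
- **Shared first month.** Study design and procedure: "Both groups receive 4 CBT group sessions in the first month". On total duration it says "patients are followed up for 6 months, for a total of 8 months", following two months of sessions.
- **Time of allocation.** Treatment groups, after describing the group sessions: "Participants are then randomized into two groups (M1".
- **Planning.** Sample size, on the 15 pilot patients: "Their cumulative alcohol consumption was monitored at two, five and eight months after admission". The purpose was "to estimate the average daily consumption over eight months". No mean difference or SD is given.
- **Primary test.** Statistical methods: "Student's t-test for independent samples". The complementary regression models adjust for the minimisation factors and the number of sessions. Drinking in month 1 is not listed as a covariate.

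**The concern.** Both arms receive the same care until M1, and nobody has been allocated. Drinks in that month therefore have an expected between-arm difference of zero, yet they are summed into the sole primary endpoint. They bring between-patient variance and no treatment signal. The primary test neither removes them nor adjusts for them. The total also absorbs a pre-allocation measure of drinking that could have served as a baseline covariate.

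What is at stake is power, in a trial planned at 80%. The start of the count is also at stake: it has to be inferred from the objective, because the outcome definition does not give it.

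**Working it through.** **1. The plan's own figure.** Inputs from Sample size: 65 per group, two-sided alpha 0.05, power 0.80. The 65 cannot be derived forward without a difference and an SD. Solved backwards, d = √(2/65) × (1.960 + 0.842) = 0.491 (0.495 by the t distribution). A conventional d of 0.5 would give 63 or 64 per group.

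**2. Share of the window before allocation.** Eight months are counted and allocation is at M1, so 1/8 = 12.5% precedes it and 7 months follow.

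**3. Effect on the SD.** Two quantities have to be assumed, since the article gives no variance data:
- ρ, the correlation between any two months, from 0 to 1;
- f, the month-1 SD as a fraction of a later month's SD, from 0.1 to 1.

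With a later month's variance set to 1:
- Var(M1–M8) = 7 + 42ρ
- Var(M0–M8) = 7 + 42ρ + f² + 14ρf
- SD ratio r = √[Var(M0–M8) / Var(M1–M8)]

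Example, f = 1:
- ρ = 0: r = √(8/7) = 1.069
- ρ = 1: r = √(64/49) = 1.143

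The mean difference is the same in both windows, so the standardised effect is multiplied by 1/r, which is 0.935 and 0.875 here.

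**4. Power on the enrolment-to-M8 total, if 65 per group gives 80% on the M1–M8 total.** Normal approximation with d = 0.491/r. The number per group for 80% is 65r², rounded up.

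| f | r (ρ = 0 to 1) | Power (ρ = 0 to 1) | Per group for 80% |
|---|---|---|---|
| 0.1 | 1.001–1.014 | 80–79% | 66–67 |
| 0.25 | 1.004–1.036 | 80–77% | 66–70 |
| 0.5 | 1.018–1.071 | 79–74% | 68–75 |
| 1 | 1.069–1.143 | 75–69% | 75–85 |

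**5. A different planning basis: a constant daily difference over all eight months.** Only 7/8 of such a difference can arise after M1. Then d = 0.491 × 7/8 = 0.430, power is 69%, and 85 per group would be needed. This is an alternative to step 4 and is not to be added to it.

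**6. The opposite planning basis: the 65 already gives 80% on the eight-month total.** This would be so if the planning SD came from the pilot's eight-month series and the planned difference was one that can arise after M1. Counting M1–M8 would then raise power to 85–89% at f = 1, 81–85% at f = 0.5 and 80–83% at f = 0.25.

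**7. Equivalence of the two fixes.** Let X be M0–M1 drinking and Y the M1–M8 total. The enrolment-to-M8 total is Y + X. In a linear model with X as a covariate, replacing Y by Y + X raises the coefficient of X by exactly 1 and leaves the residuals unchanged. The treatment estimate and its standard error are therefore identical.

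**The case against.** The strongest reply is that this is a matter of efficiency and not of validity. That stands: randomisation balances month-1 drinking in expectation, and the absolute difference in drinks is the same in either window. A reader might infer that the endpoint is biased towards no effect. The document does not support that; only the standardised and relative effects shrink.

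Second, the loss may be small. Eligibility requires at least 15 days of abstinence and excludes relapsing patients, so month-1 drinking may be low. This also stands, and it is why the low rows of the table belong in the range.

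Third, a reader might infer that true power is 69%, or that the stated 80% rests on an effect running through all eight months. Sample size describes averaging pilot consumption over eight months and a target in WHO risk levels, but gives no difference. The 69% is a worst case: it needs either the constant daily difference of step 5, or month 1 as variable as later months together with a very high correlation between months. The pilot also ran from admission, so early variability may already be in the 65.

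Fourth, the enrolment anchor is in the Introduction, while the outcome definition is silent on the start. The Secondary outcomes section describes monthly craving ratings after M2 as collected in the same way as the primary outcome, and the schedule table is not shown. Counting might in practice start later. That would then conflict with the stated objective, so the start needs stating either way.

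**Conclusion.** The point holds as a should-fix on efficiency and clarity. By the stated objective, allocation time and primary test, about one month in eight is counted before the arms can differ, and it is neither removed nor adjusted for. For any non-negative correlation between months, this raises the variance without adding signal.

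The size is not determined by the document. Starting from 80% power on the M1–M8 total at 65 per group, the loss is about 0–1 percentage points if the month-1 SD is a tenth of a later month's, and 5–11 points if they are equal. These figures rest on an assumed equal correlation between months, the assumed SD ratios and a normal approximation. Neither end of the range is established.

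**What to change.** **Preferred.** Define the primary outcome as cumulative standard drinks from randomisation (M1) to M8, and include M0–M1 TLFB drinking as a covariate in the primary model. Keep the enrolment-to-M8 total as a sensitivity outcome.

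**If the sponsor would rather not change the registered outcome.** Keep the eight-month total and replace the unadjusted t-test by a linear primary model with M0–M1 drinking as a covariate. By step 7 this gives the same treatment estimate and standard error.

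**In either case.** State in Primary outcome the date from which drinks are counted. State in Sample size whether the planned difference was spread over eight months or seven, with the difference and SD used.

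**Cost.** No new visits, data or patients, since TLFB is described as monthly. It is more than an edit of wording, however. Enrolment began in October 2023 and the trial is open-label. Research ethics approval requires sponsor agreement and a favourable ethics opinion for a substantial modification, and the registry entry would need updating if the outcome changes. The change should be made and dated before any between-arm comparison of outcomes.

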
## Methods/Design

### Study setting and population

Study data will be collected in day hospitals (DH) within the addiction departments of public hospitals. For this research, four centers in the Paris area will be involved in recruiting patients. The four recruiting centers are: 1) Department of Addictions—Hôpital Albert Chenevier—CHU Henri Mondor—APHP – Créteil, 2) Department of Addictions—Hôpital Fernand Widal—Nord—Université de Paris—APHP – Paris, 3) Department of Addictions—Centre hospitalier des Quatre Villes – Sèvres, 4) Department of Addictions—Tolbiac Day Clinic – Paris. Recruitment will be done by the investigating physician at the time of admission to the DH during an individual consultation. If the patient is eligible for the study, the full protocol will be presented and reviewed during an individual consultation at the DH enrollment visit.

The following inclusion criteria apply: i) 18 to 80 years of age at the time of enrolment; ii) patients with a diagnosis of AUD according to DSM-5 criteria (American Psychiatric Association, 2013); iii) patients who had been abstinent for at least 15 days; iv) patients who can speak, understand and read French; v) patients who have signed an informed consent form and who are affiliated to a health insurance plan.

Subjects are not included if they are: i) adults under legal protection or deprived of liberty by judicial or administrative decision; ii) pregnant or breast-feeding women; iii) patients with decompensated psychiatric disorders (psychotic disorders, mood disorders and anxiety disorders); iv) patients relapsing from their AUD; v) patients with severe cognitive impairment as defined by the MOCA Cognitive Assessment Test (score < 10) [24]; vi) visually impaired patients; vii) patients with contraindications to virtual reality exposure, due to epilepsy or history of photoparoxysmal EEG response, or vestibular disorders; viii) recent cardiovascular accident less than 3 months old, current nausea/vomiting, claustrophobia and moderate or severe myopia (greater than -3. 5 diopters); ix) patients wearing any of the following medical devices (due to the risk of interference with the virtual reality headset): pacemaker, implanted defibrillator or implanted hearing aid (non-implanted prostheses are not contraindicated if the patient agrees to remove them during VR-CET); x) participation in another study or being in the exclusion period after previous research involving human subjects; xi) and patients benefiting from State Medical Assistance (defined as access to healthcare for people in an irregular situation).

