## Discussion

The present study aims to evaluate the efficacy of VR-CET combined with CBT in the treatment of AUD in recently abstinent individuals. A recent review of the literature highlights the emergence of virtual reality as an innovative and promising tool in the therapeutic landscape [21]. Studies on the efficacy of VR-CET have mainly focused on craving, with findings such as that exposure to alcohol-related stimuli in virtual reality can increase participants' desire to drink [5]. In terms of its reduction, VR-CET appears to have positive effects, particularly for individuals with AUD [1, 41]. The perceived level of realism of the virtual environment seems to influence this efficacy, with a more pronounced reduction in the desire to drink when the environment is perceived as realistic. About anxiety, the effects of VR-CET were mixed, but integration with CBT resulted in a significant reduction in post-treatment anxiety, although less favorable than in the CBT group alone. About alcohol use, only one study examined this variable and showed that VR-CET had no significant short-term effects [42]. The systematic review highlighted the lack of longitudinal data to consolidate the efficacy of VR-CET as a therapeutic tool to reduce alcohol consumption Table 2.

Our protocol aims to address the limitations of previous research by increasing the sample size (*N *= 156), by aiming not only for abstinence but also for a reduction in consumption, which seems more realistic, by having broad inclusion criteria to allow the inclusion of a population as close as possible to clinical reality, integrating sociodemographic questions into our inclusion questionnaire, and considering comorbidities via the MINI questionnaire at inclusion. In addition, we included urinary toxicity test (ethyl glucuronide) during the two months of therapy to objectify alcohol use data. In response to previous criticism regarding the lack of virtual environments with negative connotations, two neutral environments (subway and supermarket) were included to induce a sense of stress.

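### Length of abstinence at entry has no upper limit and is in no stated analysis; using it as a baseline covariate would be a cheap gain in precision (minor)

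*Protocol article*

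**What the plan says.** - **Entry rule.** Under Study setting and population, the third inclusion criterion admits "patients who had been abstinent for at least 15 days". No maximum is given there, and none of the listed non-inclusion criteria caps the length of abstinence.
- **Population as described.** The Discussion says the study "aims to evaluate the efficacy of VR-CET combined with CBT in the treatment of AUD in recently abstinent individuals". The abstract's Context uses the same adjective, but in a sentence about gaps in earlier research. The abstract's Methods describe the sample by the 15-day minimum. The primary objective in the Introduction is to "evaluate the efficacy of a treatment strategy combining VR-CET and CBT on reducing the cumulative number of standard drinks", without reference to recent abstinence.
- **Allocation.** Treatment groups lists five factors: center, drug treatment to maintain abstinence, AUD treatment in the last five years, consumption goal and DSM-5 severity. Abstinence length is not among them.
- **Analysis.** Statistical methods compares the primary outcome by Student's t-test for independent samples. Complementary generalized linear models are "adjusted for minimization factors and number of sessions per setting".

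**The concern.** A rule with only a lower bound admits both a patient two weeks past the last drink and one who stopped many months ago. These patients may differ a good deal in how much they go on to drink over 8 months, whichever arm they are in. That difference is outcome variation that a baseline covariate could remove, and none of the stated analyses uses it.

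At stake is some precision in the treatment comparison, together with the accuracy of the population description. The Discussion's adjective promises a narrower group than the criterion delivers, so a reader of the results could apply them to the wrong patients.

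**Working it through.** **1. Is abstinence length covered anywhere in the stated plan?** Reading the sections side by side: inclusion sets a minimum only; non-inclusion sets no maximum; it is not an allocation factor; the primary test has no covariates; the complementary model takes the allocation factors and session counts. It is in none of these.

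**2. Is the information available?** The 15-day criterion cannot be applied without establishing when the patient last drank. Recording the number of days therefore adds almost nothing to the inclusion visit.

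**3. What could adjustment gain?**

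Inputs from Sample size: two-sided alpha 0.05, power 0.80, 65 evaluable per group. The section prints no mean difference or standard deviation, so 65 cannot be reproduced from its own inputs. Solving the two-sample t-test backwards for 65 per group gives the effect that the plan implies:

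- d = 0.495 (normal approximation: (1.960 + 0.842) × √(2/65) = 0.491).

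This is a back-solved value, not one the protocol states.

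Assumption: days since last drink, suitably scaled, correlates r with the drink total within each arm. The documents give no value, so a range of 0.2 to 0.4 is shown. Adjustment reduces the residual variance to a fraction 1 − r², so the effective standardised effect becomes d / √(1 − r²):

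| r | 1 − r² | effective d | power, 65 per group |
|---|---|---|---|
| 0 | 1.00 | 0.495 | 80.0% |
| 0.2 | 0.96 | 0.505 | 81.6% |
| 0.3 | 0.91 | 0.519 | 83.6% |
| 0.4 | 0.84 | 0.540 | 86.4% |

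At r = 0.4 the gain is like having 65 / 0.84 = 77 patients per group in an unadjusted test; at r = 0.2 it is like 65 / 0.96 = 68.

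**4. Where does the gain apply?** Only to an analysis that contains the covariate. The stated primary test is unadjusted, so adding the covariate to the complementary model leaves the power of the primary comparison at its planned 80%. The 82–86% would be reached only if the adjusted model were made the primary comparison.

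**The case against.** **The mismatch is mostly one sentence.** The formal objective does not say recently, the abstract's use of the word concerns earlier research, and the abstract's Methods already describe the sample by the 15-day minimum. This stands: the population point is a wording correction to the Discussion, not a flaw in the objective.

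**A reader might infer that long-abstinent patients dilute the effect and leave the trial underpowered.** The documents do not support that. They give no share of long-abstinent patients. Recruitment takes place "Recruitment will be done by the investigating physician at the time of admission to the DH during an individual consultation", which makes long-established abstinence less likely, though it does not rule it out. The 15 patients used for sizing came from the day hospital of one of the recruiting centers, and nothing says they were restricted to recent abstinence. If such patients are admitted, the planning figures may already reflect them, and diluting the planned effect again would count them twice.

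**A reader might also infer that entry needs an upper limit on abstinence.** The Discussion presents broad criteria as deliberate, to stay close to clinical reality, and a cap introduced during recruitment would mix two populations. This objection stands too.

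**The covariate may be in a document not shown.** The article condenses a full protocol, an analysis plan may exist, and the schedule table cannot be read here. It therefore cannot be said that abstinence length goes unrecorded or will never be used. It can be said that the adjustment set the article does state leaves it out.

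**Randomisation protects the comparison.** Agreed: leaving out a prognostic covariate does not bias the treatment effect in expectation.

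**Conclusion.** The point holds as a minor one. Certain from the text: entry has a 15-day minimum and no maximum, abstinence length is in neither the allocation factors nor the stated adjustment set, and the Discussion's description of the population is narrower than the criterion.

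Conditional: the gain from adjustment. A rise from 80% to about 82–86% rests on a correlation of 0.2 to 0.4, on the back-solved effect of 0.495, on 65 evaluable patients per group, and on the adjusted model serving as the primary comparison. With a correlation near zero the gain vanishes, and the cost is one degree of freedom. No loss of power from dilution and no bias is established.

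**What to change.** 1. Record days since last drink at inclusion, if this is not already done, and pre-specify it on a log scale as a baseline covariate in the adjusted analysis of the primary outcome, before any outcome data are examined by arm. Cost: one field whose content is already needed to check eligibility, and one line in the analysis plan.
2. If the precision gain is wanted for the primary comparison itself, name the adjusted model as the primary analysis in place of the unadjusted t-test, again before unblinded data are seen. This is a change to the primary analysis and has to be documented as one. Otherwise, present the adjusted result as supportive and claim no power gain for the primary test.
3. In the Discussion and in the eventual conclusion, describe the population as having 15 or more days of abstinence at entry and drop the word recently. Report the distribution of abstinence length by arm in the baseline table, so that readers can see who was studied. Cost: wording and one table row.

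No change to the eligibility criteria or the sample size is needed on this ground.
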